## Abstract

**Background:**

Cognitive dysfunction is a major feature of bipolar disorder with psychosis and is strongly associated with functional outcomes. Computer-based cognitive remediation has shown promise in improving cognition in patients with schizophrenia. However, despite similar neurocognitive deficits between patients with schizophrenia and bipolar disorder, few studies have extended neuroscience-based cognitive remediation programs to this population.

**Methods/Design:**

The Treatment to Enhance Cognition in Bipolar Disorder study is an investigator-initiated, parallel group, randomized, blinded clinical trial of an Internet-based cognitive remediation protocol for patients with bipolar disorder I with psychosis (*n* = 100). We also describe the development of our dose-matched active control paradigm. Both conditions involve 70 sessions of computer-based activities over 24 weeks. The control intervention was developed to mirror the treatment condition in dose and format but without the neuroplasticity-based task design and structure. All participants undergo neuropsychological and clinical assessment at baseline, after approximately 25 hours of study activities, post treatment, and after 6 months of no study contact to assess durability. Neuroimaging at baseline and post treatment are offered in an “opt-in” format. The primary outcomes are scores on the MATRICS battery; secondary and exploratory outcomes include measures of clinical symptoms, community functioning, and neuroimaging changes. Associations between change in cognitive measures and change in community functioning will be assessed. Baseline predictors of treatment response will be examined.

**Discussion:**

The present study is the first we are aware of to implement an Internet-based cognitive remediation program in patients with bipolar disorder with psychosis and to develop a comparable web-based control paradigm. The mixed online and study-site format allows accessible treatment while providing weekly staff contact and bridging. Based on user-provided feedback, participant blinding is feasible.

**Trial registration:**

ClinicalTrials.gov NCT01470781; 11 July 2011.

## Background

Cognitive impairment is common in patients with bipolar disorder (BD) and is associated with poorer functional outcomes [1–5] and longer time to recovery after a first episode [6]. Over time, increasing illness burden appears to be associated with increased neurocognitive dysfunction [7]. Despite strong associations between cognitive impairment and functional outcomes, treatment for these symptoms is inadequate. Medications produce modest overall improvement in cognitive symptoms, and may even worsen some aspects of cognition [8–11]. As few as one third of patients achieve functional recovery over time [12]. At least partial disability is reported in approximately 80 % of patients with BD; as many as 65 % of patients report being unemployed even after clinical recovery, and patients experience significant disability in daily living and social functioning [13]. As cognition is among the strongest predictors of functional outcomes (e.g., [3, 4]), and consistent with a European College of Neuropsychopharmacology expert report [13], it is critical to target this key symptom dimension in patients with BD [1, 4, 12, 13].

### Cognitive deficits in bipolar disorder

Patients with BD exhibit deficits in memory, executive function, and processing speed/efficiency that persist during euthymic phases and over time [14–18]; patients with BD with a history of psychosis (BDP) may be especially cognitively impaired [14, 19, 20]. Cognitive remediation (CR) is a promising treatment approach addressing neurocognitive dysfunction in the hopes that improved cognitive performance will translate to better community outcomes. A meta-analysis of 40 studies of CR for adults with schizophrenia (SZ) found that these programs produced moderate, durable effects on cognitive functioning [21]. A recent meta-analysis of 16 studies reported moderate effects of CR on cognition in affective illness (primarily affective psychosis) similar to findings in SZ [22]. Despite the substantial overlap in cognitive impairments between SZ and BD – qualitatively and in some studies quantitatively – only one study to date has reported outcomes after CR in patients with BD. In a 14-session cognitive training program focusing on neurocognitive deficits and residual symptoms of depression in patients with BD, CR was associated with improved executive functioning, which was related to improved vocational performance [23].

### Challenges in cognitive remediation

Typical CR paradigms require multiple training sessions weekly, which may be prohibitive for potential study participants. Many of the CR programs that have shown efficacy in patients with SZ have studied chronic patients who are able to attend sessions at community-based programs multiple times per week, due to high levels of disability and low instrumental role involvement (e.g., [24]). While patients with BD exhibit considerable disability, especially compared to premorbid functioning, patients with SZ or schizoaffective disorder (SZA) exhibit greater morbidity and disability on average [25], indicating that treatments requiring multiple weekly sessions at study sites may be unrealistic, especially for patients who are even partially engaged in work or school roles. With rapid advancements in online cognitive training programs, there is considerable potential for Internet-based treatments to improve access to training for patients. However, reports suggest that face-to-face “bridging” sessions, which create an opportunity for subjects to explicitly consider implementation of newly-developed cognitive skills in daily life, are important for generalizing the effect of CR treatments to daily functioning [26]. Thus, a tension exists between reducing participant burden through remote access and conducting treatment delivery in the most effective manner.

Inclusion of adequate comparison conditions is challenging in CR paradigms given the active nature of the treatment. “Placebo” conditions are particularly challenging with these types of programs, as participants are keenly aware of the elements of participation throughout the program. The majority of projects that have included an active control group have selected individual or group rehabilitative or therapeutic activities such as Enriched Supportive Therapy [27], supportive group therapy [28], cognitive behavioral therapy (CBT) [29], Integrated Psychological Therapy [30], treatment as usual plus group activities [31], vocational rehabilitation, occupational therapy, supported employment [32–34], computer skills training plus day treatment [35] or social skills training [36]. These types of comparison conditions allow for the control of hours of study staff contact and other factors associated with involvement/adherence to a psychosocial intervention; however, they do not control for other aspects of the CR intervention such as computer interaction or game engagement, and they do not reasonably permit double-blindness – a particular challenge for interpretation of results as poor masking of treatment allocation in clinical trials has been shown to inflate treatment effects [21].

Recently several game-format comparison conditions have been developed for CR paradigms attempting to match the computer/gaming elements of CR but with nonspecific content; these include computer games or action videogames [24, 37–39], some paired with additional group or coaching activities to match for other elements of the active treatment condition [37, 38]. No studies to date have published findings including Internet-based controls that can be overseen via remote access; however, as Internet-based CR programs are in active development and use, comparable Internet-based paradigms that will permit active comparison are needed.

CR programs vary considerably in terms of methodology, and it is not clear which if any aspect(s) of treatment design influence outcomes. Variables to consider include total duration of treatment, number of sessions, treatment intensity (i.e., “density” of sessions), drill and practice approaches versus strategy use, and individual versus group format, among many other characteristics. A meta-analysis of 40 CR studies did not find any effect of treatment characteristics on cognitive outcomes [21], although programs that included strategy use showed a trend toward greater functional improvements [21, 40].

Finally, it is possible that participant characteristics may influence treatment response. In their meta-analysis, Wykes and colleagues [21] found no effect of most baseline characteristics including age, baseline cognitive functioning, or chlorpromazine equivalents on outcomes after CR; however, lower clinical symptoms at baseline were associated with greater effects of treatment on cognitive outcomes.

In this report we aimed to (1) describe our Internet-based neuroplasticity-informed CR protocol for BDP, (2) describe the development of our Internet-based, dose-matched active control, and (3) assess the ability of our study design to remain blinded.

## Methods/Design

This study and all associated procedures comply with the ethical standards of the relevant national and institutional committees on human experimentation and with the Helsinki Declaration of 1975, as revised in 2008, and have been approved by the McLean Hospital Institutional Review Board. This project is registered with ClinicalTrials.gov (NC01470781), and all procedures and reporting of our primary and secondary outcomes will follow Consolidated Standards of Reporting Trials (CONSORT) 2010 guidelines [41].

### Participants

Outpatients with idiopathic BD Type I with a history of psychosis between the ages of 18 and 50 (*n =* 100) are recruited through the McLean Hospital Psychotic Disorders Program and fliers posted at the hospital (See Fig. 1). All participants are informed of the study procedures, including randomization to either treatment or control conditions, and provide written informed consent. All patients are symptomatically stable outpatients at the time of enrollment, and have been out of the hospital for at least 1 month with Positive and Negative Syndrome Scale (PANSS) scores under 75, ratings of 3 (mild) or less on the PANSS psychosis items, and Young Mania Rating Scale (YMRS) scores below 6. We set these criteria based on findings that baseline clinical symptoms are associated with treatment response [21]. To reduce medication confounds, only patients on monotherapy lithium or valproate plus an atypical antipsychotic (excluding clozapine) are eligible. Patients taking anticholinergic medications are excluded, as they produce cognitive dysfunction and may interfere with CR response [42, 43]. Exclusion criteria include: substance abuse in the past month; substance dependence in the past year; history of seizure disorder or head injury with loss of consciousness; anticholinergic medications (e.g., benztropine), clozapine, and topiramate.

**Fig. 1 Fig1:**
[figure not shown]
Consolidated Standards of Reporting Trials (CONSORT) 2010 flow diagram: Treatment to Enhance Cognition in Bipolar Disorder Allocation and study flow

### Power calculation

For the total sample, we aim to recruit 100 participants, which will yield approximately 50 participants per group. This sample size is based on power calculations using a conservative estimate of effect size of two thirds of the effects on cognition of published findings using similar duration and paradigm CR in patients with SZ (*d* = 0.74–0.89) [24, 44] and anticipating attrition at approximately 15 % [44]. One-tailed alpha for sample-size estimates was selected because directional effects are hypothesized (CR greater than control intervention) and have been established in other populations. Thus, with alpha at 0.05 we have 80 % power to detect effects of 0.54 or greater.

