### Procedures

Randomization was started using a simple randomization approach, but due to increasing imbalance this approach was switched to a blocked random design with a block size of 10. The Research Randomizer tool (www.Randomizer.org) was used to generate the random allocation sequence. The principal investigator (PI), [name], generated the sequence, which was given to enrollment staff who are responsible for group assignment. We employed a parallel design with an allocation ratio of 1:1. The randomization key is kept by a single staff member, who provides the treatment and/or communicates assignment information directly to treatment staff. Assessment staff are not informed of group assignment (see below). Participants are not informed of their group assignment. During the consent process participants are explicitly informed that participation in the study involves random assignment to either the treatment condition or an active control, that they may be assigned to the control condition, and that they will not be informed of their group assignment. Participants are informed that they may request knowledge of their study assignment at the end of the follow-up period.

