### Statistical approach

Our primary aim is to evaluate the effect of CR on cognition in patients with BDP compared to a computer-based control. The primary outcome measures of interest are MCCB scores. Primary analyses will be based on composite scores; secondary analyses will examine domain scores if composite findings are significant. The main analysis will be an intent-to-treat analysis, which includes all randomized subjects regardless of compliance to reduce potential for post-randomization bias and inflation of Type I errors. We will use a linear mixed effects model; inclusion of random effects accounts for the correlation among repeated measures. Outcome measures will include the three post-baseline measures of cognition; the baseline measure will be adjusted for by including it as a covariate. The test of no treatment difference will be based on a joint test of the group and group-by-time interaction.

The secondary aim is the examination of potential mechanisms for changes in community functioning. It is hypothesized that cognitive (but not clinical) change will mediate changes in community functioning. Thus, community functioning will be modeled adjusting for composite neuropsychological (or clinical) change using linear mixed effects models to relate changes in community functioning to treatment group while adjusting for differences in cognitive (or clinical) change.

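### The stated 80% power at d = 0.54 belongs to a one-tailed single contrast, not to the non-directional joint test planned as the primary analysis

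*Protocol article*

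**What the plan says.** In the Protocol article, the Power calculation section gives the planned size: "we aim to recruit 100 participants, which will yield approximately 50 participants per group". The effect is taken as "two thirds of the effects on cognition of published findings using similar duration and paradigm CR in patients with SZ", with the published effects given as d = 0.74–0.89, and attrition is put at about 15%. On sidedness it says: "One-tailed alpha for sample-size estimates was selected because directional effects are hypothesized". It concludes: "Thus, with alpha at 0.05 we have 80 % power to detect effects of 0.54 or greater". It names no test, number of visits or correlation.

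The Statistical approach section fixes the primary analysis as a linear mixed effects model on the three post-baseline MCCB composite scores, with the baseline score as a covariate. On the hypothesis test it says: "The test of no treatment difference will be based on a joint test of the group and group-by-time interaction". The Procedures section confirms 1:1 allocation.

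**The concern.** The two sections describe different tests. A power figure with one standardised effect and a one-tailed alpha presupposes a single contrast with a sign. A joint test of group and group-by-time asks whether any of several coefficients differs from zero. It rejects for benefit, for harm, or for a difference in time pattern, and it has no one-tailed form. The reason given for the one-tailed alpha, a directional hypothesis, therefore cannot carry over to the planned test.

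The article's case for 100 participants rests on this paragraph. A null result would be judged against 80% power that was never shown for the test performed. The mismatch also leaves room for a later argument over whether the primary claim rests on a one-tailed contrast or on the joint test.

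**Working it through.** **Inputs from the Protocol article.** 100 randomised 1:1 and 15% attrition give 85 completers, or n = 42.5 per arm. Alpha is 0.05 and d = 0.54. The planning range is 2/3 × 0.74 = 0.493 to 2/3 × 0.89 = 0.593, with midpoint 0.543.

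**Step 1: reproduce the stated figure.** For a two-group comparison on one contrast, the noncentrality is d × √(n/2) = 0.54 × √21.25 = 2.489.

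- One-tailed, normal approximation: Φ(2.489 − 1.645) = 80.1%. The detectable effect at 80% power is (1.645 + 0.842) × √(2/42.5) = 0.539.
- One-tailed, noncentral t with 83 df: 79.5%, detectable effect 0.544.
- In reverse, 43 per arm are needed; 86/0.85 = 101.2, or 102 as an even total, close to 100.

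Variants that do not reproduce it (noncentral t): one-tailed with 50 per arm, 85.0%; two-sided with 50 per arm, 76.2%; two-sided with 42.5 per arm, 69.2% (detectable effect 0.615). The stated figure is thus a one-tailed single contrast among completers. That it is a t-test or similar is inferred from this match, since the article names no test.

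**Step 2: the planned test.** With time as a factor, group plus group-by-time over three visits has 3 df; with linear time it has 2. Power comes from a noncentral F with noncentrality λ = (n/2) × δ′Σ⁻¹δ, where δ holds the standardised group differences at the three visits and Σ is their correlation matrix.

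The article gives neither δ nor Σ, so these are my assumptions: unit SD, one correlation r between all visits, 80 denominator df, and four effect profiles (midpoint / post-treatment / follow-up). The value 0.19 is 25/70 of 0.54, the share of the training hours done by the midpoint. With baseline credit, the baseline correlation is set equal to r, d is read on the raw-SD scale, and Σ becomes Σ − r²·11′.

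For a constant effect, λ = 6.20 × 3/(1 + 2r) without baseline credit and 6.20 × 3/(1 + 2r − 3r²) with it, where 6.20 = 21.25 × 0.54². At r = 0.5 these are 9.30 and 14.87.

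Power of the 3-df test, without / with baseline credit (%):

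| Profile | r = 0.3 | r = 0.5 | r = 0.7 | r = 0.8 |
|---|---|---|---|---|
| 0.54 / 0.54 / 0.54 | 80.6 / 87.9 | 70.3 / 90.0 | 61.5 / 96.8 | 57.6 / 99.5 |
| 0.27 / 0.54 / 0.54 | 71.6 / 79.0 | 66.1 / 83.3 | 67.8 / 94.1 | 74.4 / 98.8 |
| 0.19 / 0.54 / 0.54 | 72.0 / 78.5 | 69.7 / 84.0 | 76.3 / 95.0 | 85.5 / 99.2 |
| 0.27 / 0.54 / 0.27 | 54.2 / 61.1 | 51.1 / 67.0 | 55.9 / 83.1 | 65.1 / 94.1 |

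The ranges are about 51–85% without baseline credit and 61% to over 99% with it.

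**Step 3: a single contrast as the alternative.** Two-sided and unadjusted, power is 69% at d = 0.54, and 80% is reached at d = 0.61. With baseline adjustment the effective d is 0.54/√(1 − r²). At r = 0.5 this is 0.624, and two-sided power is 81%.

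**The case against.** The arithmetic in the Power calculation section is right on its own terms. The one-tailed choice is disclosed, explained and confined to the sample-size estimate. A simple unadjusted calculation is common, and it can be conservative for a richer model. The planned analysis uses three visits, a baseline score on the same battery and partially observed data. If d is on the raw-SD scale, high visit correlation with no gain from baseline is implausible; with baseline credit and r of 0.7 or more, every 3-df case in the table exceeds 80%. A condensed article may also leave correlations and effect profiles to the full protocol. All of this stands, and it limits the point to a mismatch: nothing in the article connects the quoted 80% to the planned test, and both the power premise and the test are stated in the article itself.

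Three stronger readings are tempting and not supported:

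- **The trial is underpowered.** The ranges lie on both sides of 80%, and the inputs that would decide are not given.
- **Power of the joint test is 51% (3 df) or 58% (2 df).** Those values arise if the noncentrality of one unadjusted visit is spread over 3 or 2 df. They ignore the other visits and the covariate, so they do not describe the planned test either. (The 51% in the table is a different calculation, for one unfavourable profile over three visits.)
- **The lower end of the planning range, 0.493, falls below 0.54 and so contradicts the claim.** The stated 0.54 is the midpoint of that range, and powering for a midpoint is ordinary practice.

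**Conclusion.** The point holds as a mismatch between the sample-size method and the primary analysis, not as an arithmetic error. The 80% at d = 0.54 is the power of a one-tailed single contrast with about 42.5 completers per arm. The planned joint test is non-directional with 2 or 3 df, so its power has not been stated. The ranges in the table rest on assumed equal correlations and assumed effect profiles; their spread shows that the figure cannot be settled from the article, and it is not evidence of a shortfall. The type I error and validity of the primary test are not affected. What is affected is the stated justification for 100 participants and the standard against which a null result would be read.

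**What to change.** Choose one of two routes.

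1. Keep the joint test as primary. Replace the one-tailed statement with the power of that test at 5%, and state the assumed visit correlation, baseline correlation and effect profile across the three visits.
2. Make a one-df contrast primary, for example the baseline-adjusted post-treatment difference, and state its sidedness and power. Two-sided and unadjusted, the article's inputs give 69% at d = 0.54 and 80% at d = 0.61. With the baseline covariate the power is higher, and the assumed correlation should be stated. These two-sided figures should be quoted only on this route; beside the joint test they would repeat the mismatch.

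The cost is a short recalculation and one rewritten paragraph, plus, on the second route, a change to the primary test that should be dated and made before any unblinded analysis. No extra patients are needed. The restated power may be less favourable than 80%. With 76 participants enrolled by July 2015 against a target of 100, there was still time to make the correction during recruitment.

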### Assessment measures

#### Cognition

Cognitive functioning was assessed using the battery developed by the Measurement and Treatment Research to Improve Cognition in Schizophrenia (MATRICS) initiative [45]. While the MATRICS Consensus Cognitive Battery (MCCB) was developed for cognitive assessment in SZ, the MCCB has been validated in patients with BD [46, 47]. The MATRICS battery includes 10 tasks that measure processing speed (Brief Assessment of Cognition in Schizophrenia Symbol Coding, Animal Fluency, Trails A), attention (Continuous Performance Test), working memory (WMS-III Spatial Span, Letter-Number Span), verbal learning (Hopkins Verbal Learning Test – Revised), visual learning (Brief Visuospatial Memory Test – Revised), problem solving (Neuropsychological Assessment Battery Mazes) and social cognition (Mayer-Salovey-Caruso Emotional Intelligence Test). Total administration time is 60–90 minutes.

#### Clinical and community functioning

Clinical and community functioning assessment included: the Positive and Negative Syndrome Scale (PANSS; [48]); Young Mania Rating Scale (YMRS; [49]); Montgomery-Asberg Depression Rating Scale (MADRS; [50]); Multnomah Community Ability Scale (MCAS; [51]); Social and Occupational Functioning Assessment Scale (SOFAS; [52]). The MCAS measures functioning in psychiatric patients in multiple domains (e.g., social effectiveness, independence, meaningful activities). The SOFAS is a 100-point scale similar to the Global Assessment of Functioning that evaluates social and occupational functioning not directly influenced by symptom severity.

